### Data management and monitoring

Work training was held before the start of the project to provide detailed explanation of the trial protocol, standard operating procedures (SOPs) for study operations, and the content of case report forms (CRFs). Investigators will record the results faithfully on the CRFs. Data will be entered in the EpiData 3.1. system. Any incomplete data will be classified as missing or not applicable.

The Clinical Trial Centre Office of the Eye Hospital of Wenzhou Medical University will be responsible for data monitoring and overseeing the whole study. The original data, including private information, baseline data, orthoptic therapy outcome data, follow-up data, and statistical analysis result data will be kept in the Data Monitoring Committee, which is an important department in Clinical Trial Centre Office. The original data set will not be granted to the public. Data will be shared as requested after approval by the Clinical Trial Centre Office. Any relevant publications will be shared with clinical researchers who have interest. Due the relative simple design of the study procedure and a moderate funding, we considered that a formal auditing plan was not required.

### Safety monitoring

To protect the rights and interests of patients, all participants and their guardians will be informed of the potential benefits and possible risks of the trial before they enrol. The whole process will be carried out in a separate and quiet room by a trained professional assistant (JL). After confirming that the patient and guardian understand the relevant content, we will ask both the patient and his or her guardian to sign an informed consent form. If any one of these individuals do not sign the informed consent form, they will not be admitted to the study.

Because the orthoptic therapy being used in our study is a form of functional training, which is a non-invasive operation, the risk of harm to patients is very small. However, we will still inform all individuals of the training process in detail and will give them the researcher’s telephone or WeChat to communicate at any time. If any care is needed post-trial, we will provide professional care service.

### Statistical analysis

Statistical analysis will be performed using SPSS software version 20.0 (IBM Corp., Armonk, NY, USA). The parameters to be calculated are the means ± standard deviations for the continuous variables and the rates (proportions) for the categorical variables.

For the primary analysis, the cumulative proportion of participants meeting the criteria for suboptimal surgical outcomes by 2 years will be compared between the 2 groups using the Kaplan-Meier method. An intergroup difference and a corresponding 95% confidence interval (CI) will also be calculated. Each of the 2 individual components of the specified suboptimal surgical outcome criteria will be assessed using the chi-square test.

For all IXTs who completed the 24-month follow-up, changes in exodeviation measured by PACT, stereoacuity, exotropia control score, accommodative amplitude and facility, and fusional convergence amplitude between baseline and the 24 months will be compared between the two groups in linear regression models that will be adjusted for the corresponding baseline values. Additionally, considering that binocular visual function is different in different age, the final data may be divided into two subgroups according to different ages.

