**Methods:**

A total of 136 IXT patients (aged 7 to 17 years) will be enrolled and assigned to the orthoptic therapy group or blank control group according to a simple randomization scheme. Patients in the orthoptic therapy group will receive at least 2 months of orthoptic therapy, such as anti-suppression, vergence, and accommodation training. Patients in the blank control group will receive only refractive correction. All enrolled patients will need regular follow-up observation until 24 months after surgery. The primary outcome will be the proportion of participants meeting suboptimal surgical outcomes in this 24-month follow-up, which is defined as (1) exodeviation of 10 prism diopters (PD) at distance or near using the simultaneous prism and cover test (SPCT) or (2) loss of 2 or more octaves of stereoacuity from baseline, at any masked follow-up visit examination. The secondary outcomes will be the exodeviation at distance and near using the simultaneous prism and alternate cover test (PACT), magnitude of fusional convergence, stereoacuity, and accommodation. Measurements will be taken at baseline and at the 6-, 12-, 18-, and 24-month follow-ups.

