### Tests performed at baseline and each follow-up visit

After obtaining consent and assent, health-related quality of life (HRQOL) will first be assessed using the Intermittent Exotropia Questionnaire (IXTQ) [25]. It will be completed by each participant and their guardians in separate and quiet rooms. Then, each participant will undergo comprehensive ophthalmic examinations, including best corrected visual acuity (BCVA), subjective refraction, slit-lamp biomicroscopy, and fundus examination. Then, strabismic and binocular visual examinations will be performed, including stereopsis, the amplitude of fusional vergence at far and near, monocular and binocular accommodative amplitude, monocular and binocular accommodative facility, near point of convergence, the prism and alternate cover test (PACT) and simultaneous prism and cover test (SPCT). The examination will first test for binocular and then monocular functions without breaking fusion. If the fusion is broken, for example, the monocular items will be used first for examination. The present study includes a baseline visit and 6-, 12-, 18-, and 24-month follow-up visits. Each examination will be completed on the same day. The 4 follow-up visits will fall into a ± 2-week range. The HRQOL will be completed at the first and last examinations. To ensure the quality and repeatability of data acquisition, we will ask two experienced clinicians to perform all testing procedures; they will be blind to the patient’s randomization status. The standard process regarding the important test items is as follows:

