#### Control group therapy

For the participants in the control group, all binocular visual function tests will also be completely performed at each follow-up visit. If refractive status changes, appropriate prescription will be provided and used in a pair of new glasses.

If only binocular visual function deterioration occurs, it is proposed that they continue to be observed; if accompanied by a small angle of exodeviation but not meeting the criteria of suboptimal surgical outcome or if participants ask for visual function therapy, they will have deviated from the study protocol and will be considered to be dropped out of group. If eye position regression is obvious and the definition of recurrence is reached, he or she will be classified as having a suboptimal surgical outcome. They will be offered a reoperation to align the eye position or start orthoptic therapy during the study.

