### Sample size

Sample size calculation is based on the expected value of efficacy from previous studies. The proportion of participants meeting suboptimal surgical outcomes is 16.7% [20] in surgery combined with orthoptic therapy group and 36.5% in surgery alone [21]. We hypothesis that there will be a significant difference in the cumulative proportion of suboptimal surgical outcome at 24 months after surgery between our two groups. We set the statistical power was set at 80% with a type 1 error probability (alpha) of 0.05 based on a 2-tailed chi-square test. The theoretical sample size was 61, with a 1:1 sample ratio. After allowing for a maximum dropout rate of 10% during the 2-year follow-up, we found that the estimated the sample size for each group to reach a statistical significance was 68.

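### The two components of the primary outcome are tested by chi-square, which cannot use partial follow-up, while the composite itself is analysed by Kaplan-Meier

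*Protocol article*

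**What the plan says.** In the protocol article, Statistical analysis, the cumulative proportion with a suboptimal surgical outcome by 2 years "will be compared between the 2 groups using the Kaplan-Meier method", and a between-group difference with 95% CI is to be given. The same paragraph continues: "Each of the 2 individual components of the specified suboptimal surgical outcome criteria will be assessed using the chi-square test". The components are exodeviation of at least 10 PD on SPCT at distance or near, and loss of at least 2 octaves of stereoacuity. The abstract counts either one if met "at any masked follow-up visit examination", so both are cumulative over the 6-, 12-, 18- and 24-month visits.

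Three other sections bear on who is observed to 24 months:

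- **Sample size** allows for at most 10% dropout over the two years.
- **Criteria for dropout** makes a control who starts any non-surgical treatment a dropout. In the therapy arm, stopping training or training irregularly is expressly no reason for withdrawal.
- **Control group therapy** also treats as dropouts controls who ask for therapy, or whose functional decline comes with a small exodeviation short of the criterion. Of controls who meet the criterion it says: "They will be offered a reoperation to align the eye position or start orthoptic therapy during the study".

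**The concern.** One endpoint is given two methods that treat incomplete follow-up differently. Kaplan-Meier keeps a child in the risk set up to the last visit attended. A chi-square test on a cumulative yes/no outcome cannot, so each child lost before 24 months without an event becomes either a success or a deletion. The first choice biases the proportion down and the second biases it up.

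Because some dropout rules apply only to controls and run throughout follow-up, loss may differ between arms, and the bias need not cancel in the difference.

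The components also meet a problem that the composite does not. Once a control has failed on one component and had reoperation or therapy, the composite event is already recorded, but later status on the other component is altered by treatment.

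The component results tell the reader whether any benefit lies in alignment, which is the primary objective, or in stereopsis. They should be on the same footing as the composite.

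**Working it through.** The article gives no component rates and no figure for the component tests, so there is nothing of that kind to reproduce. The dropout allowance does reproduce: 61 / (1 − 0.10) = 67.8, rounded up to 68 per group. Whether 61 follows from the stated test is a separate question and is not used here.

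**Inputs from the article**
- 24-month proportions p = 16.7% (therapy) and 36.5% (control), from Sample size. They are composite rates, used as stand-ins. A component rate cannot exceed the composite rate in the same arm.
- Dropout D = 10%, from Sample size.
- Four visits: "The present study includes a baseline visit and 6-, 12-, 18-, and 24-month follow-up visits".

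**Assumptions**
- D = 20% as an alternative, and 10% therapy with 20% control as an unequal case.
- Equal risk of first failure at each visit.
- Dropout spread evenly over the four intervals and unrelated to outcome.

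**Formulas**
- Risk of failure per visit: h = 1 − (1 − p)^(1/4)
- Risk of loss per interval: d = 1 − (1 − D)^(1/4)
- q = (1 − d)(1 − h) and g = (1 − q⁴)/(1 − q)
- Lost children counted as event-free: C₀ = (1 − d)·h·g
- Lost before any event: L = d·g
- Lost children deleted: C₁ = C₀/(1 − L)
- Kaplan-Meier on scheduled visits: a fraction h of those attending is expected to fail at each visit, so the estimate targets 1 − (1 − h)⁴ = p, whatever D is.

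**Worked case, control arm, D = 10%**
- h = 1 − 0.635^(1/4) = 0.1073
- d = 1 − 0.90^(1/4) = 0.0260
- q = 0.9740 × 0.8927 = 0.8695 and q⁴ = 0.5715
- g = 0.4285/0.1305 = 3.283
- C₀ = 0.9740 × 0.1073 × 3.283 = 34.3%
- L = 0.0260 × 3.283 = 8.5%
- C₁ = 34.3/0.915 = 37.5%

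**All cases**

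| Arm (true value) | D | Lost = event-free | Lost deleted |
|---|---|---|---|
| Therapy (16.7%) | 10% | 15.7% | 17.3% |
| Control (36.5%) | 10% | 34.3% | 37.5% |
| Therapy (16.7%) | 20% | 14.6% | 18.0% |
| Control (36.5%) | 20% | 32.1% | 38.7% |

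A simulation with 68 per arm and 1,500 runs per setting agrees to within about 0.2 points. In it, Kaplan-Meier on scheduled visit times gave 16.5–16.7% and 36.5–36.6% at every dropout level.

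**Differences** (true value 36.5 − 16.7 = 19.8 points)
- 10% in both arms: 34.3 − 15.7 = 18.6, or 37.5 − 17.3 = 20.2
- 10% therapy, 20% control: 32.1 − 15.7 = 16.4, or 38.7 − 17.3 = 21.4. The simulated values give 32.1 − 15.5 = 16.6 and 38.8 − 17.2 = 21.6.

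In the unequal case the choice of counting rule alone is worth about 5 points. The effect of treatment after a first failure is not included.

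**The case against.** The component tests are supportive. With no losses, Kaplan-Meier on scheduled visits equals the crude proportion, so the methods part only through dropout, and at the planned 10% the gap is small. The denominator of the chi-square, and how a component is counted after a first failure, are details that an article may leave to the analysis plan. Loss among controls is probably related to prognosis, and Kaplan-Meier assumes that it is not. All of this stands. It limits the size of the point, but the article does state the chi-square, and the choice does not suit its own dropout rules.

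Three stronger readings are tempting and are not supported:

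- A reader might infer from "The 4 follow-up visits will fall into a ± 2-week range" that Kaplan-Meier will run on actual visit dates and so misstate the 24-month proportion. The article never says so. The range describes scheduling, and the time scale may be left to the analysis plan. On scheduled times there is no material bias.
- A reader might infer that a reoperated child is counted as free of the other component. The article says only that reoperation or therapy is offered. It does not say that examinations stop or how the child is counted.
- A reader might want the other component treated as a competing event. A child failing first on alignment could then never count as a stereoacuity failure, which would hide the result that the analysis is meant to show.

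**Conclusion.** The point holds for the component analyses. The stated chi-square is inconsistent with the method stated for the composite and handles the expected losses badly. The shift is about 0.5 to 2 points per proportion at 10% dropout and about 1 to 4.5 points at 20%. In the assumed unequal case, a 19.8-point difference becomes about 16.5 or 21.5. These sizes rest on composite rates standing in for component rates, an equal risk at each visit, and dropout unrelated to outcome. Lower component rates would generally give smaller shifts. The primary Kaplan-Meier analysis is not shown to be wrong.

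**What to change.** Replace the chi-square sentence with the composite's method:

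- For each component, analyse time to its first occurrence on the scheduled visit scale (6, 12, 18, 24 months), with children lost censored at their last attended visit.
- Report the 24-month cumulative proportion per arm, the difference and its 95% CI.
- Count a child who meets both components, at the same or different visits, in both. Do not make one component a competing event for the other.
- State how reoperation or therapy begun after a first failure is handled for the remaining component, as a competing event or by censoring, with a sensitivity analysis using the other approach.

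Naming scheduled visit times for the composite as well would be a useful clarification, not a correction. The cost is a change of wording and slightly more analysis, with no new data. It does not remove bias from informative dropout, which needs its own sensitivity analysis.

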### Criteria for dropout

The criteria of dropout will be (1) patients in orthoptic therapy group who did not accept training with 2 weeks of enrolment, (2) patients in control group who had started any kind of postoperative non-surgical treatment (e.g., patching, orthoptic training), (3) participants who had requested to be withdrawn from the study. All participants will be permitted to withdraw or terminate the study for any reason during the study, and the reasons will be recorded. Discontinuation or irregular orthoptic therapy will not be a reason for withdrawal from the study, and participants could complete follow-up visits provided if they are willing.

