#### Primary outcome

The primary outcomes in our study will be the cumulative proportion of participants meeting suboptimal surgical outcomes at 24 months after surgery; these suboptimal outcomes are defined as (1) exodeviation of ≥ 10 PD at distance or at near using SPCT or (2) loss of 2 octaves or more of stereoacuity from baseline.

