#### Secondary outcomes

The secondary outcomes in our study include the following items: the exodeviation at near and distance tested by PACT, fusional convergence amplitude, stereoacuity, accommodative amplitude, and facility.

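### Comparing the secondary outcomes at 24 months in completers only, after control failures have been offered retreatment, biases exodeviation towards no difference and can reverse it if uptake is high

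*Protocol article*

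**What the plan says.** Secondary outcomes lists "the exodeviation at near and distance tested by PACT, fusional convergence amplitude, stereoacuity, accommodative amplitude, and facility". Statistical analysis adds the exotropia control score and fixes three things: the set ("For all IXTs who completed the 24-month follow-up"), the contrast (baseline to 24 months) and the model. The changes "will be compared between the two groups in linear regression models that will be adjusted for the corresponding baseline values".

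Control group therapy says of controls who meet the definition of recurrence: "They will be offered a reoperation to align the eye position or start orthoptic therapy during the study". The same section says of controls whose functional decline comes with a lesser exodeviation, or who request therapy, that "they will have deviated from the study protocol and will be considered to be dropped out of group". Criteria for dropout includes "patients in control group who had started any kind of postoperative non-surgical treatment (e.g., patching, orthoptic training"; reoperation is not on that list.

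For the therapy group, the only arm-specific dropout criterion is not taking up training within two weeks of enrolment. Stopping training or training irregularly is expressly no reason for withdrawal. No offer of retreatment after failure is described for that group.

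**The concern.** Read together, these sections send a control failure who accepts the offer down one of three routes. After reoperation, the participant can still complete 24 months and enters the comparison with a surgically corrected angle. After starting orthoptic therapy, the participant leaves the set as a dropout or, if kept because the therapy was offered within the study, is measured after the experimental treatment. Each route improves or removes a poor control value.

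The process depends on outcome and is described for one arm only. It arises after randomisation, so adjusting for the baseline value cannot correct it. The measurements at 6, 12 and 18 months, which would show the state before retreatment, are not used in this comparison.

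The Background makes the gain in binocular function the trial's second question, and these regressions are the analysis given for it. A therapy that works could show too small a benefit, or none, on the secondary measures.

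**Working it through.** The article states no figure for the secondary analysis, so there is none to reproduce. The check asks how far the planned analysis can move a known difference.

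**Inputs from the document.** Failure proportions are 36.5% (surgery alone) and 16.7% (with orthoptic therapy), with 68 per group (Sample size). Expected failures are 68 × 0.365 = 24.8 controls and 68 × 0.167 = 11.4 therapy participants, so those affected are mostly controls.

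**Assumed inputs.** The article gives no mean deviations and no uptake of reoperation. Illustration: mean exodeviation at 24 months of 6 PD without failure, 15 PD after untreated failure and 3 PD after reoperation. Baselines are taken as equal by randomisation, so a difference in means equals a difference in change.

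**Mixture model.** With failure proportion p and reoperated share r among failures:

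mean = p × [3r + 15(1 − r)] + (1 − p) × 6

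- Therapy group, r = 0: 0.167 × 15 + 0.833 × 6 = 7.50 PD.
- Control, r = 0: 0.365 × 15 + 0.635 × 6 = 9.29 PD. Control minus therapy = **+1.8**, favouring therapy.
- Control, r = 0.5: 0.365 × 9 + 0.635 × 6 = 7.10 PD. Difference **-0.4**.
- Control, r = 1: 0.365 × 3 + 0.635 × 6 = 4.91 PD. Difference **-2.6**.
- Sign change: each unit of r lowers the control mean by 0.365 × (15 − 3) = 4.38 PD, so r = 1.78 / 4.38 = **0.41**.
- All control failures start therapy and are removed: the control mean is 6.00 PD. Difference 6.00 − 7.50 = **-1.5**.

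**Range of assumptions.** Non-failures 3 to 5 PD, failures 12 to 20 PD, 0 to 5 PD after reoperation:

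| Handling of failures | Control minus therapy (PD) |
|---|---|
| No retreatment | +1.4 to +3.4 |
| Half of control failures reoperated | -0.8 to +0.6 |
| All control failures reoperated | -4.3 to -0.8 |
| All control failures removed | -2.8 to -1.2 |
| All failures in both arms reoperated | -1.0 to +0.4 |

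With reoperation in controls only, the sign changes at 32% to 70% uptake.

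**Less extreme model.** Exodeviation is normal with SD 6 PD, failure means exceeding 10 PD, and the arm means are set to give the planned proportions: 10 − 6 × 0.345 = 7.93 (control) and 10 − 6 × 0.966 = 4.20 (therapy).

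- True difference: 7.93 − 4.20 = **+3.7**.
- All control failures reoperated to a mean of 3 PD: control non-failures average 4.38, so the control mean is 0.635 × 4.38 + 0.365 × 3 = 3.88. Difference **-0.3**.
- Half reoperated: (7.93 + 3.88) / 2 = 5.90. Difference **+1.7**.
- All control failures removed: 4.38 − 4.20 = **+0.2**.
- All failures in both arms reoperated (simulated): **+1.4**.

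In every scenario the difference moves towards zero or past it.

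**The case against.** A reader might infer that the secondary results can be expected to contradict the primary one. The documents do not support that. The deviations and uptake are assumptions. In the continuous model half uptake still leaves +1.7 PD, and only full control-only uptake turns slightly negative. Two features also soften the effect:

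- A failure first seen at month 24 has a 24-month value from before any retreatment, so full uptake before that measurement would need every failure to be detected by month 18.
- The failure definition has two limbs: "exodeviation of ≥ 10 PD at distance or at near using SPCT", or a loss of two or more octaves of stereoacuity. Participants who fail on stereoacuity alone may have little exodeviation, so giving every failure 15 PD overstates both the true difference and the reset.

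A reader might also infer that the trial's main conclusion is at risk. It is not, on this point. The Kaplan-Meier analysis counts a participant once the criterion is met, and later surgery or therapy cannot undo that event.

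It can further be said that a 24-month comparison including values after retreatment answers a legitimate question, and that detailed handling is often left to a statistical analysis plan. Both are fair. But the article itself fixes the completer restriction and the time point. Dropping controls who start therapy also means the planned set does not deliver an all-values comparison.

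The limits on size, the unaffected primary outcome and the legitimacy of an all-values analysis therefore stand. The one-sided mechanism stands as well.

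**Conclusion.** The concern holds as a bias in the secondary comparisons, shown here for exodeviation only. Stereoacuity, fusional convergence and accommodation share the completer set and time point, but no size was worked out for them. The direction is towards the null. Reversal is a possibility that needs high uptake among control failures with no matching retreatment in the therapy group: about 41% in the illustration, 32% to 70% across the mixture assumptions, and close to full uptake in the continuous model.

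The asymmetry rests on the offer appearing only under Control group therapy. If failures in the therapy group are retreated alike, the effect is smaller: -1.0 to +0.4 PD in the mixture range, and +1.4 of +3.7 PD retained in the continuous model. This should be fixed because it is cheap to fix.

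**What to change.** **Main secondary analysis.** Replace the completer regression with a baseline-adjusted repeated-measures mixed model in all randomised participants with any follow-up. Use the 6-, 12-, 18- and 24-month values, with the 24-month contrast as the estimate. Values up to and including the failure visit stay in; values after reoperation, or after a control starts orthoptic therapy, are set aside.

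**Sensitivity analyses.**
- (a) A rank analysis in which everyone who met the suboptimal outcome is scored worst, in either arm and whatever retreatment was chosen. Scoring only reoperated participants worst would favour therapy, because reoperation is described only for controls.
- (b) An analysis of all observed 24-month values regardless of retreatment.

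**Text to reconcile.** Control group therapy offers orthoptic therapy after failure within the study, while Criteria for dropout makes a control who starts it a dropout. The two must be brought into agreement so that the analysis set is defined.

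**Cost.** Revised wording and a little more programming; the visits are already scheduled. The model assumes that values after retreatment are missing at random given the earlier ones, and the sensitivity analyses probe that assumption.
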